## Abstract

**Background:**

The proportion of older people has dramatically increased in recent decades. Moreover, social and demographic trends show a global increase of older people at risk of loneliness and lack of social relationships. The objective of this study was to evaluate the process, the effectiveness and the cost-effectiveness of a planned 22 weekly group sessions called School of Health for Older People to reduce social isolation.

**Methods:**

This is a mixed methods multi-approach evaluation that includes: 1) A qualitative evaluation among coordinators and participants taking part in the intervention, through in depth-interviews and focus groups, respectively. The main topics covered will be positive and negative aspects of the intervention, suggestions for its improvement, opinions on different aspects of the intervention, and perceived benefits; 2) A quantitative quasi-experimental design, comparing a group of individuals taking part in the intervention with another group with similar characteristics not receiving the intervention. Data will be collected at the beginning and at the end of the intervention. Social support will be measured through questions drawn from the Medical Outcomes Study and the National Social Life, Health, and Aging Project questionnaires. Psychological morbidity will be measured through Goldberg’s General Health Questionnaire, and Health-related Quality of Life will be measured through the EuroQoL questionnaire. Information on visits to the primary care center in the years before and after the intervention will be obtained from the electronic records of the primary care centers; 3) A cost-utility analysis, which will be conducted from a health system (primary care) perspective, including direct costs of the program and the primary care health services used. The effects of the intervention will be measured on quality-adjusted life years.

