## Hypothesis

The intervention evaluated in this protocol will significantly improve social support, mental health, general health status and distinct dimensions of quality of life in the intervention group (IG) compared with the comparison group (CG). Among participants in the IG, the intervention will also significantly reduce the number of visits to their primary care centers. Furthermore, this intervention will be cost effective.

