#### Quantitative quasi-experimental design

The study population will consist of adults aged 65 years or older residing in the disadvantaged neighborhoods of Barcelona (Spain) selected for the study. The intervention neighborhoods (*n* = 2) and comparison neighborhoods (n = 2) will be selected on a convenience basis, ensuring similar socioeconomic characteristics, including the percentage of people with primary studies or less, unemployment rates and disposable household income rates.

The intervention will be offered to adults aged 65 years or older, living in one of the two selected neighborhoods, and recruited through primary care centers, social services and civic centers for older people. Once individuals have accepted to participate, there will be a pre-registration process that will record their names and telephone numbers. Later, the participants will be contacted by telephone to arrange an appointment, in which the person will be informed individually about the study. After agreement, he/she will sign the informed consent form and complete a questionnaire.

To calculate the sample size, we took into account that 45% of people aged 65 years or more in Barcelona reports fair or poor health [21] and assumed that the intervention would reduce this prevalence by 17 points. Accepting an alpha risk of 0.05% and a power of 80% in a unilateral contrast, and assuming a loss of 10%, we estimated that a theoretical sample of 79 participants in the IG and 79 participants in the CG will be needed.

We expect to recruit 80 individuals in the IG and 80 in the CG. To have similar groups, the recruitment settings (primary care centers, social services and civic centers) would be taken into account, by selecting the same percentage of people from each setting.

The exclusion criteria are the following:Participants with difficulties in maintaining participation for 6 months.Participants with difficulties in understanding or expressing themselves in Spanish or Catalan.

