#### Quantitative quasi-experimental design

##### Main outcomes

Social support will be measured through questions taken from the Medical Outcomes Study: Measures of Quality of Life Core Survey (MOS) [22] and NSHAP questionnaires [20]. Psychological morbidity will be measured through Goldberg’s General Health Questionnaire (GHQ-12) [23], and health-related quality of life will be measured through the EuroQoL (EQ-5D) questionnaire [24]. Objective information will be obtained on visits to the primary care center during the year before and after the intervention through access to the electronic records of the primary care centers.

All these variables will be measured simultaneously in individuals in the IG and CG. Data will be collected through baseline and post-intervention questionnaires administered by trained researchers.

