#### Quantitative quasi-experimental design

A descriptive analysis will be conducted to rule out significant differences between baseline characteristics (sociodemographic variables and outcomes studied) in the IG and the CG. The chi-square test will be used to compare qualitative variables. Continuous variables with normal distribution will be compared using the Student t test, and the Mann-Whitney U test will be used in non-normally distributed variables. In case of differences, a further multivariate effectiveness analysis will be conducted adjusting for these variables.

Further descriptive analyses will be conducted for results at baseline and at follow-up. Categorical outcomes will be described through percentages, and continuous outcomes will be described through mean scores and standard deviations or the median and interquartile range, as required. Differences between pre- and post-intervention measurements will be assessed and compared using the McNemar test, paired t-test, or sign test, according to the type of variable and distribution.

To assess the effectiveness of the intervention, a two-sample McNemar test will first be conducted to analyze differences in changes in pre- and post-intervention results between the IG and the CG for each main outcome. In those outcomes showing differences between the groups at the baseline measurement, Poisson regression models with robust variance will be built. In each model, the independent variables will be the group (IG or CG), the pre-intervention measurements for the outcome assessed and any relevant characteristics that differ between the groups at the baseline assessment.

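### Primary care visits are compared on one year before and one year after the programme, so in a non-randomised design a yearly total gives no check on whether visits in the two groups were already diverging

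*Protocol article*

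**What the plan says.** Visits to the primary care centre are listed among the main outcomes. The protocol article's Main outcomes section sets the window as "visits to the primary care center during the year before and after the intervention", obtained "through access to the electronic records of the primary care centers". The Abstract words it differently: "Information on visits to the primary care center in the years before and after the intervention will be obtained from the electronic records". The Hypothesis section expects that, in the IG, "the intervention will also significantly reduce the number of visits to their primary care centers".

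There are two intervention and two comparison neighbourhoods. According to the quantitative design under Study setting and participants, they "will be selected on a convenience basis, ensuring similar socioeconomic characteristics"; the characteristics named are education, unemployment and household income. Past visit levels and trends are not among them.

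The Data analysis section compares pre-post changes between groups and tests for baseline differences. It then states: "In those outcomes showing differences between the groups at the baseline measurement, Poisson regression models with robust variance will be built", with the pre-intervention value as a covariate. Strengths and limitations accepts that the groups may differ and relies on the same baseline comparison and adjustment.

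**The concern.** Comparing changes between non-randomised groups attributes to the programme whatever difference in trend already existed. Adjusting for baseline level does not remove this. Two groups can have the same visit level in the baseline year while one is rising and the other falling; the planned baseline tests would then find no difference and no adjustment would follow.

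The position of the baseline year adds to this. Some participants are recruited through primary care centres, and the only pre-period is the year that ends at enrolment. If people join after a year of unusually high use, part of any later fall is regression to the mean. Taking the same share from each recruitment setting helps, but does not ensure that the effect is equal in people who join a 22-week programme and people in the CG. The hypothesis, framed as a reduction in the IG, is exposed to exactly this.

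At stake is the interpretation of the one main outcome that does not depend on self-report.

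**Working it through.** **Is there a figure to reproduce?** No. The sample size rests on self-rated health ("45% of people aged 65 years or more in Barcelona reports fair or poor health", and it was "assumed that the intervention would reduce this prevalence by 17 points"). The protocol gives no mean, SD or year-to-year correlation for visits. The correlations below are therefore assumptions, in units where the yearly SD is 1.

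**Step 1: can a trend be checked?** A trend within a group needs at least two time points. One yearly total before the programme gives one point per group, which leaves zero degrees of freedom for comparing pre-programme trends.

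**Step 2: how far apart are the windows?** Participant timeline puts the intervention in January to June 2015.
- Year before: about January to December 2014, midpoint 1 July 2014.
- Year after, counted from the end of the programme: about July 2015 to June 2016, midpoint 1 January 2016.
- Distance between midpoints: 1.5 years.

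Spurious effect = trend difference × distance. With an illustrative 0.5 visits per year: 0.5 × 1.5 = 0.75 visits. If the year after were instead counted from the programme's start, the distance would be 1.0 year and the shift 0.5 × 1.0 = 0.5 visits.

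**Step 3: what would earlier years add in precision?** The fix uses prior counts as covariates, so the relevant quantity is the residual variance of the post-year given the pre-years (linear approximation). With one pre-year and correlation r it is 1 − r².

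*(a) Equal correlation r between all years.* With k pre-years the residual variance is 1 − k·r²/(1 + (k − 1)r).

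| r | 1 pre-year | 3 pre-years | change |
|---|---|---|---|
| 0.3 | 0.910 | 0.831 | −9% |
| 0.5 | 0.750 | 0.625 | −17% |
| 0.8 | 0.360 | 0.262 | −27% |

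*(b) Correlation that fades with distance.* With one pre-year at r = 0.60 the residual variance is 1 − 0.36 = 0.640. For the mean of three pre-years it is 1 − (mean correlation with the post-year)² / (variance of the pre-year mean).
- Stronger fading: correlations with the post-year 0.60, 0.52, 0.45; among pre-years 0.65 (adjacent) and 0.55 (two apart). Variance of the mean = (3 + 2(0.65 + 0.65 + 0.55))/9 = 0.744. Mean correlation = 1.57/3 = 0.523. Residual = 1 − 0.523²/0.744 = 0.632 (−1%). With each year as its own covariate it is 0.605 (−5%).
- Milder fading: 0.60, 0.56, 0.53; among pre-years 0.62 and 0.58. Variance of the mean = (3 + 2(0.62 + 0.62 + 0.58))/9 = 0.738. Mean correlation = 1.69/3 = 0.563. Residual = 1 − 0.563²/0.738 = 0.570 (−11%). With each year as its own covariate it is 0.564 (−12%).

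*(c) AR(1).* Once the latest year is in the model, earlier years carry no further information: the residual variance stays at 0.750 for r = 0.5 and 0.510 for r = 0.7, whether one, two or three pre-years are used.

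Entering each year separately does at least as well as the mean in every case here, which is why the fix prefers it.

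**The case against.** One year on each side is a common, seasonally balanced choice, and nothing in it is stated wrongly. Four stronger readings are tempting, and the document does not support them.

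- *The Abstract proves a single-year baseline, or flatly contradicts Main outcomes.* It does neither. Its plural may only mean the year before and the year after. The single year rests on Main outcomes; the difference is a matter of wording to align.
- *Earlier years are in the records and cost nothing.* The article does not say how far back the records reach, whether all centres hold older data, or what period consent and ethics approval cover. Availability is plausible, but it is an assumption.
- *The baseline is needlessly noisy, by 25% with two pre-years or 33% with three, as if there were 120 instead of 80 per group.* Those figures follow from (1 + 1/k)(1 − r) against 2(1 − r). They hold only for an unadjusted change score with correlation that never fades. With the baseline as a covariate the gain is smaller. Under AR(1), averaging pre-years even raises the change-score variance (r = 0.7: 0.60 with one year, 0.73 with three).
- *Diverging trends cannot be seen at all.* If dated visits are extracted, the single year could be split into months or quarters. The article does not say. One seasonal cycle is still a poor basis for a trend.

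Three further limits stand. No divergence is shown; the 0.5 visits per year is illustrative. Two neighbourhoods per arm give little basis for testing parallel trends, however many years are added. The economic evaluation has a 6-month time frame, so a bias in the yearly visit windows does not carry directly into its costs.

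What the objection does not remove is that the stated safeguards address level only, and a single yearly total cannot speak to trend.

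**Conclusion.** The point holds as an inexpensive design improvement, not as an error in a stated figure. With one yearly pre-period total, the plan has no means of telling a programme effect on visits from a trend difference already under way, and its adjustment for baseline differences does not address this. The size is conditional: 1.5 times whatever yearly trend difference exists, or 0.75 visits for an illustrative 0.5 per year, taking the year after to start when the programme ends.

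The main gain from earlier years is the check on trend and on an atypical baseline year. The precision gain is secondary and uncertain. With three pre-years and the baseline as covariate, the variance falls by 9 to 27% under equal correlation (r from 0.3 to 0.8), by 1 to 12% under the two fading patterns (5 to 12% if each year is entered separately), and by nothing under AR(1). All these figures rest on assumed correlations.

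**What to change.** 1. Give the visit window the same wording in the Abstract and in Main outcomes, with dates, and say whether visits are extracted by date or as yearly totals.
2. Where the electronic records and consent allow, extract dated or yearly visit counts for two to three years before January 2015, for both IG and CG participants.
3. Enter each prior year as a covariate in the count model for visits. As written, the regression is built only when groups differ at baseline, so state that it is used for visits in any case.
4. Before interpreting the change, report the pre-programme trend by group as a descriptive check, and say that it can reveal diverging trends but, with two neighbourhoods per arm, cannot establish that they are parallel.

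Cost: a somewhat wider data request, possibly a check of consent and ethics coverage, and a little more analysis. Some participants will have incomplete histories, for example because they moved recently, and the plan should say how these are handled. No additional participants or questionnaires are needed.

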**Discussion:**

There is an urgent need for studies assessing the effectiveness and the efficiency of potential interventions to reduce social isolation among older persons. The results of this study will help to fill the knowledge gap in this area and might be especially useful for the development of social and public health policies and programs for older people in disadvantaged neighborhoods in urban areas.

**Trial registration:**

NCT03142048 retrospectively registered (April 11, 2017).

## Background

The proportion of older people has dramatically increased in recent decades [1]. In the city of Barcelona, 21.2% of the population is 65 years or older, and projections indicate that this percentage will increase to 23.9% in 2031 [2].

Social and demographic trends show a global increase of older people at risk of loneliness and lack of social relationships. This may be due to certain aging-related factors such as retirement or the loss of a partner or close friends [3]. Previous studies have found higher rates of loneliness in deprived urban areas [4]. Furthermore, other studies have found that some of the variables significantly associated with loneliness in older adults included poor income and lower educational level [5], and that living in a deprived area adds barriers to social engagement [6]. Overall, recent studies confirm that rural residents reported less social isolation and more social relationships than urban residents [7]. Therefore, disadvantaged urban areas need to be studied, and evaluated interventions in these areas should be prioritized.

Social relations are associated with good mental health, while their absence is linked to a significant increase in morbidity and mortality [8–10]. Because of its high prevalence and the evidence of its impact on health and wellbeing, social isolation is an important public health issue.

Based on the aforementioned evidence, interventions are needed to reduce social isolation and its negative effects on quality of life. Although preventing and addressing social isolation in older people is a priority in health policies, there is a clear lack of evidence on the effectiveness of health promotion activities in this field, as well as wide heterogeneity in the interventions and their quality [11–15].Therefore, studies evaluating the effectiveness of interventions designed to reduce the impact of social isolation on wellbeing and quality of life in older people are much needed. Detailed protocols on how to evaluate this complex interventions can help to standardize the evaluation across interventions and homogenize the evidence on this area. In this sense, this protocol might be useful as a tool for future interventions to be evaluated.

Since 2008, an intervention called the “Schools of Health for Older People” has been implemented in some deprived neighborhoods of Barcelona. This intervention is part of the comprehensive action *Health in the neighborhoods* [16], focused on reducing health inequalities in the city of Barcelona by implementing community interventions in the most deprived neighborhoods. The main goal of the “Schools of Health for Older People” is to reduce social isolation in this collective, as well as its potential harmful health effects. As shown in numerous studies [17, 18], these effects can be especially important in low-income older people. The main objective of this protocol is to describe the mixed methods multi-approach evaluation study designed to assess this intervention.

## Hypothesis

The intervention evaluated in this protocol will significantly improve social support, mental health, general health status and distinct dimensions of quality of life in the intervention group (IG) compared with the comparison group (CG). Among participants in the IG, the intervention will also significantly reduce the number of visits to their primary care centers. Furthermore, this intervention will be cost effective.

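### The primary care visits hypothesis is worded as a fall within the intervention group only, and the plan guarantees no between-group test that fits a visit count

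*Protocol article*

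**What the plan says.** In the Hypothesis section, social support, mental health, general health status and "distinct dimensions of quality of life in the intervention group (IG) compared with the comparison group (CG" are set as between-group contrasts. The next sentence treats visits apart and names no comparator: "Among participants in the IG, the intervention will also significantly reduce the number of visits to their primary care centers".

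Under Outcome measures, Main outcomes, the plan obtains "visits to the primary care center during the year before and after the intervention through access to the electronic records", and adds: "All these variables will be measured simultaneously in individuals in the IG and CG".

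Under Data analysis, Quantitative quasi-experimental design, a paragraph introduced as descriptive says: "Differences between pre- and post-intervention measurements will be assessed and compared using the McNemar test, paired t-test, or sign test". The following paragraph, on effectiveness, says that "a two-sample McNemar test will first be conducted to analyze differences in changes" between IG and CG for each main outcome. Poisson regression with robust variance, adjusted for the pre-intervention value, is added only for outcomes that differ between groups at baseline.

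On selection, the neighborhoods "will be selected on a convenience basis, ensuring similar socioeconomic characteristics", and participants are "recruited through primary care centers, social services and civic centers for older people".

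**The concern.** The two hypothesis sentences use different standards of evidence. Read literally, the visits sentence is satisfied by a significant fall from the year before to the year after in the IG, even if visits in the CG fell by as much. The year-before and year-after records make that before-after reading a natural one.

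Two things other than the intervention can produce such a fall. One is a general change in primary care use between the two years. The other is regression to the mean: people met at a primary care center are more likely to be in a spell of high use, and such spells tend to pass. A concurrent comparison group recruited in the same way is the design's protection against both, so the hypothesis and the test for this outcome should use it.

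**Working it through.** **1. Which named method fits the number of visits?**

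| Method named in Data analysis | Contrast | Takes a count? | When used |
|---|---|---|---|
| McNemar | pre-post | no, binary | descriptive paragraph |
| Paired t, sign test | pre-post | yes | descriptive paragraph |
| Student t, Mann-Whitney | IG v CG | yes | baseline characteristics only |
| Two-sample McNemar | IG v CG change | no, binary | each main outcome |
| Robust Poisson with pre-value | IG v CG | yes | only if the outcome differs at baseline |

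The multivariate adjustment mentioned after the baseline comparison is likewise conditional on a difference. If baseline visits are similar, the only named tests of change that accept a count are therefore the pre-post paired t and sign tests.

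**2. How often would the Poisson model be built?** The plan gives no distribution for visits. Assumed here: mean 10 visits a year, gamma variation between people (shape 2), independent gamma variation between years (shape 4), 80 per group, baseline compared by Mann-Whitney at 5%, 3000 runs. The model is triggered in about 5% of studies when true baseline rates are equal, and in 9%, 20% and 36% at true baseline rate ratios of 1.1, 1.2 and 1.3.

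**3. How large could regression to the mean be?** The plan has no figure for visits to reproduce, and its sample size rests on self-rated health. As a pure illustration, let mean m = 10 and SD s = 7, with entry strictly proportional to prior-year visits.

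- Prior-year mean among entrants: m + s²/m = 10 + 49/10 = 14.9.
- Next-year mean: m + r × s²/m = 10 + 4.9r, where r is the year-to-year correlation.
- r = 0.5: 12.45, a fall of 2.45. r = 0.6: 12.94, a fall of 1.96. r = 0.7: 13.43, a fall of 1.47.

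This is the extreme case, with every entrant selected on attendance. The fall shrinks with the share recruited without regard to attendance.

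**4. What would each test do with no intervention effect?** The distribution is that of step 2. It implies variance 10 + (150 × 1.25 − 100) = 97.5, so SD about 9.9, and correlation 50/97.5 = 0.51. This is more dispersed than step 3. There are 72 completers per group (80 less the plan's 10% loss), both groups are recruited the same way, and w is the share of recruitment weight proportional to prior-year visits. Each setting has 1000 runs. Entries are the proportion of studies declaring a reduction at two-sided 5%, so nominal 2.5%.

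| Setting | Mean change in IG | Paired t, IG | Sign test, IG | Change, IG v CG |
|---|---|---|---|---|
| w = 0 | 0.02 | 2.2% | 2.4% | 2.4% |
| w = 0.25 | −1.24 | 13.1% | 8.7% | 3.8% |
| w = 0.5 | −2.23 | 34.3% | 23.0% | 2.9% |
| w = 1 | −4.50 | 77.3% | 74.2% | 2.2% |
| w = 0, visits fall 5% generally | −0.45 | 5.8% | 4.6% | 2.3% |
| w = 0, visits fall 10% generally | −1.02 | 14.5% | 11.4% | 2.9% |
| w = 0, visits fall 15% generally | −1.49 | 27.5% | 20.4% | 1.8% |

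The formula of step 3 gives 9.75 × (1 − 0.51), about 4.75, for w = 1. This is close to the simulated fall of 4.50.

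**The case against.** The strongest reply is that the protocol already intends a between-group comparison. Visits are a main outcome, they are recorded in the CG, and effectiveness is defined as the IG-CG difference in change for each main outcome. The within-group tests stand in a paragraph labelled descriptive. The hypothesis sentence may only be saying whose visits the intervention can affect, since only the IG receives it. All of this stands. A reader might infer that the CG visit data go unused, or that the plan adopts a within-group test as its effectiveness test. The documents do not support either. What remains is a conflict between the Hypothesis section and the later sections, and an intended comparison with no fitting test attached.

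Visits might also be dichotomised, which would make the two-sample McNemar test usable, and an article can leave such detail to an analysis plan. But the hypothesis concerns the number of visits and no cut-point is given. The mismatch is general to that test and not peculiar to visits, yet here it leaves the comparator missing from the hypothesis unrepaired.

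On size, the objection is right. No eligibility rule selects on visits, two of the three recruitment routes lie outside primary care, and no shares are given. A reader might take the falls and error rates above as estimates for this trial. They are not, and with no selection and no general decline the within-group test keeps its nominal level.

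A reader might also infer that the fault passes into the cost-utility analysis. It does not: that analysis subtracts CG costs from IG costs.

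**Conclusion.** The point holds as an inconsistency with a practical consequence. The visits hypothesis is stated within the IG only, against the protocol's own two-group design, and no IG-versus-CG test suited to a count is assured unless baseline visits differ. A fall in the IG from a general decline or regression to the mean could therefore be read as confirming the hypothesis.

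That conclusion rests on the text alone. Its size rests wholly on assumption: under the distributions above, 2% to 77% false declarations within the IG against 2% to 4% between groups. The between-group result also assumes that the two groups are recruited alike. The protocol supports this in part by planning the same percentage from each recruitment setting, but convenience selection of neighborhoods means that it cannot be taken for granted.

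**What to change.** Restate the visits hypothesis as a greater reduction in visits in the IG than in the CG.

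For this outcome, name a Poisson (or negative binomial) regression with robust variance on following-year visits, with group and prior-year visits as covariates, fitted whether or not baseline visits differ. Report the within-IG change as description only.

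The cost is one sentence in the Hypothesis section and one in Data analysis. The Poisson model is already named and visit records for both groups are already planned, so no new data are needed. The change deals with what is common to both groups; it does not remove confounding from the non-random choice of neighborhoods.
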